### Objectives

The key research question of this trial is whether implementing smart home technology–enabled self-management and care delivery can maintain or improve the impact of care provided by aged care service providers to older people living independently in their own homes.

The aims of the trial were to evaluate the impact of implementing an innovative home care service delivery model via technology on: (1) the impact of care provided by aged care service providers in response to needs arising from physical or sensory impairments for older people living independently in their homes; (2) quality of life for older people living independently in their own homes; (3) factors associated with ADL and instrumental activities of daily living (iADL); (4) depression in older people living independently in their own homes; (5) health service utilization, including presentation to hospital (admitted and emergency department), attendances to general practitioners, and other Medicare-funded community health services; (6) existing model of care, service design, adoption, and aged care service provider experiences; (7) carer burden (informal carers); and (8) costs to the government as a result of deployment of the SSH platform.

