#### Primary Outcome

The primary outcome was the Australian Community Care Outcome Measurement tool (ACCOM) [27].

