### Sample Size

The primary outcome of this trial, the impact of community care for older people, will be evaluated using the ACCOM tool [27], a set of measures of community care suitable for use in the Australian context. The ACCOM mainly uses questions from the Adult Social Care Outcome Toolkit (ASCOT) [33], which is a validated measure of social care related to quality of life. Power was based on a randomized trial design with a clinically important difference of 10% on the primary outcome of ASCOT with a mean 0.80 (SD 0.16) distribution (ie, 0.08, based on previous research [33]). With the threshold of rejecting the null hypothesis of *α*≥.05, effect size of 0.5 (0.08/0.16), and the same allocation ratio of the two groups in our trial. Figure 3 illustrates the relations between total sample size and statistical power.

To achieve 80% statistical power, we needed a total of 134 participants. Allowing for a 30% attrition rate, the sample size of this trial was computed to be 200 participants. We did not anticipate an attrition rate greater than 30% as all participants were existing clients of the participating aged care service providers and received regular visits throughout the trial period. The intervention and outcome measurement collection processes were designed to minimize participant burden. In addition, the power analysis did not consider the repeated-measures design of the trial. Repeated measures increase the power of the trial to find a significant result and appropriate statistical techniques will be applied to ensure that all data available are used in the analyses.

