#### Survey Data Analyses

At each survey time point, intergroup differences in survey results between the intervention and control groups will be analyzed by *χ*^2^ tests and Wilcoxon rank-sum tests. If significant differences in survey results are observed, a log-binomial regression model will be further used to estimate the relative risk of each group to changes of survey results. Within each group, for all three surveys, the Friedman nonparametric test will be used to understand intragroup differences in survey results. Similarly, if significant differences in survey results are observed, the Wilcoxon signed-rank test with Bonferroni correction will be used to further investigate pairwise differences between surveys.

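### For ACCOM, the only between-arm estimate the plan names is a relative risk fitted after a significant test: off the 0.08 design scale, and absent when the test is null

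*Protocol article*

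**What the plan says.** All references are to the protocol article.

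- **Primary Outcome:** "The primary outcome was the Australian Community Care Outcome Measurement tool (ACCOM"). Table 2 describes it as eight attributes, each on four levels, with ASCOT scoring.
- **Sample Size:** the trial is powered on a "clinically important difference of 10% on the primary outcome of ASCOT with a mean 0.80 (SD 0.16) distribution", that is 0.08, giving an "effect size of 0.5 (0.08/0.16), and the same allocation ratio of the two groups in our trial". It adds: "To achieve 80% statistical power, we needed a total of 134 participants".
- **Objectives:** the key question is whether the technology "can maintain or improve the impact of care provided by aged care service providers". No margin is given.
- **Survey Data Analyses:** at each survey, arms are compared by chi-square and Wilcoxon rank-sum tests. Then: "If significant differences in survey results are observed, a log-binomial regression model will be further used to estimate the relative risk". The sentence goes on to tie the relative risk to changes in survey results, but does not say what change counts as an event. The other analyses in the section (Friedman, then signed-rank with Bonferroni) are within-arm.
- **Cost-Effective Analysis:** QALYs are derived from EQ-5D-5L for an incremental ratio, with no significance condition.

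**The concern.** Three things go wrong for the primary outcome if the rule is followed as written.

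1. **Scale.** A log-binomial model needs a yes/no outcome. ACCOM is a score, and no event is defined for it. A relative risk cannot be set against 0.08, the difference the trial itself calls clinically important.
2. **Silence after a null test.** A non-significant comparison yields no effect size and no interval. That is where a claim that care was maintained would need one.
3. **Selection.** Estimates that appear only when p is below 0.05 are, on average, too far from the null.

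At stake is whether the primary result can be read against its own target, and whether a null result can be told apart from an uninformative one.

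**Working it through.** **Inputs.** Sample Size: mean 0.80, SD 0.16, difference 0.08, 80% power, 134 evaluable, 30% attrition, 200 planned. Results: 195 recruited. Assumptions: scores are normal with equal SD, and the test is two-sided at 0.05. The article does not state sidedness, but two-sided reproduces its figure.

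**Step 1. Reproduce 134.** d = 0.08/0.16 = 0.5. The normal formula gives 63 per arm (126) and the t-test gives 63.77, so 64 per arm (128). Dividing by the rank-sum efficiency 3/π = 0.955 gives 63.77/0.955 = 66.8, so 67 per arm = 134, an exact match. Then 134/0.70 = 191.4, so 192, and 200 covers it. The stated test and the sample size agree; the problem lies in the estimate.

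**Step 2. Scale.** Take a true shift from 0.80 to 0.88 and an assumed cut c. Then RR = P(score > c | mean 0.88) / P(score > c | mean 0.80):

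| Assumed cut | Intervention | Control | RR |
|---|---|---|---|
| 0.5 | 99.1% | 97.0% | 1.02 |
| 0.6 | 96.0% | 89.4% | 1.07 |
| 0.7 | 87.0% | 73.4% | 1.18 |
| 0.8 | 69.1% | 50.0% | 1.38 |
| 0.9 | 45.0% | 26.6% | 1.69 |

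The cuts are illustrations and none is in the article. The same 0.08 gives anything from 1.02 to 1.69, so without a stated event the relative risk cannot be mapped back to 0.08.

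**Step 3. Selection.** Simulation: 67 per arm, 20,000 runs per row, mean difference kept only if the rank-sum p < 0.05.

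| True difference | Runs significant | Mean difference when significant | Ratio to truth |
|---|---|---|---|
| 0.08 | 80% | 0.089 | 1.12 |
| 0.06 | 56% | 0.079 | 1.31 |
| 0.04 | 28% | 0.072 | 1.79 |

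Analytic check at 68 per arm (195 × 0.7 = 136.5, taken as 136): SE = 0.16 × √(4/136) = 0.0274.

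- True 0.08: 0.08/0.0274 = 2.92 and power is 83%. The mean given significance is 0.08 + 0.0274 × φ(0.96)/0.83 = 0.08 + 0.0274 × 0.253/0.83 = 0.088, about +10%.
- True 0.04: power is 31% and the mean given significance is 0.071, about 1.8-fold.

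A relative risk at an assumed cut of 0.8 is affected in the same way: 1.38 becomes 1.45 when the true difference is 0.08, and 1.20 becomes 1.41 when it is 0.04.

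**Step 4. How often there is no estimate.** In the same simulation, about 20% of trials give none when the true difference is 0.08 (100% − 80%), and about 95% give none when it is zero.

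**Step 5. What an unconditional estimate would show.** 95% CI half-width = 1.96 × 0.16 × √(4/134) = 0.054; with 136 it is also 0.054. An observed 0.08 gives 0.026 to 0.134. An observed 0 gives −0.054 to 0.054, which excludes 0.08 in either direction.

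**The case against.** The best defence is that this is a condensed article, that a fuller analysis plan may exist, and that nothing bars the investigators from also reporting means and intervals. Sample Size promises suitable techniques for the repeated measures. That stands to this extent: the plan does not state a mean difference, which is weaker than saying the trial cannot report one. It does not remove the point. The condition on significance is a rule the article states, and the promise in Sample Size names no model or estimate.

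A reader might infer more than the text supports:

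- **That power is lost by dichotomising.** It is not. The rank-sum test remains the between-arm test for scores, the relative risk only follows it, and 134 matches that test.
- **That no survey outcome has an ungated estimate.** EQ-5D-5L has one in part, through incremental QALYs.
- **That the cut would be chosen after seeing p.** The article says when the model is fitted, not when the event is defined. The sequence leaves that risk open but does not state it as an intention. For GDS, Table 2 prints thresholds (>5 and >10), and it prints score bands for Katz, though the model is not tied to either.
- **That the plan would read p > 0.05 as care maintained.** The article never says so, and Expected Findings speaks of improvement. What holds is that the stated analysis leaves 'maintain' with nothing to rest on.

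**Conclusion.** The point holds for ACCOM, Katz, Lawton and GDS. For the primary outcome, the stated plan gives no estimate on the scale that sized the trial, and none at all after a non-significant test. When an estimate does appear, it is selected on significance.

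The inflation is modest (about 10 to 12%) if the true difference is 0.08 and large (about 1.8-fold) if it is 0.04; the larger figure should not be quoted without that condition. Both are for a mean difference, used here because the event for the relative risk is undefined. All sizes rest on normal scores with SD 0.16 and 67 to 68 analysed per arm. A bounded or skewed score would change the figures but not the direction. The test, the 134 and the economic analysis are not in question.

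**What to change.** 1. Delete the condition that estimation follows only a significant test.
2. Always report the ACCOM difference, intervention minus control at 12 months, with a 95% CI, and read it against 0.08. Report Katz, Lawton and GDS whatever their p-values too.
3. Report a relative risk only for a cut-off fixed in advance, such as the printed GDS >5, and whatever the p-value. The choice of model for it is secondary.
4. State the primary claim as 'improve'. Make no claim of 'maintain' from p > 0.05; allow it only from the CI against a margin the sponsor justifies. The 0.08 should not be borrowed as that margin without argument, because it is the trial's clinically important difference. With a half-width of 0.054, an observed loss of 0.025 would give a lower limit of −0.079 and pass a −0.08 margin while the interval reached almost a clinically important loss.

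**Cost.** No new data are needed. Null outcomes will be shown with their intervals. Because the Results section says the final analysis is underway, the change must be dated and documented, with a statement of whether the analysts were still blinded when it was made.

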### Collaborations With Consumers

In addition to the aged care service providers, the project team was fortunate to have the input of a consumer representative (ie, a person with a lived experience in this area of aging). The consumer representative also attended monthly project meetings and was able to provide guidance on how participant information should be written and delivered, how professionals should approach research participants, and provide the lived experience viewpoint to the research. Unfortunately, the consumer representative ceased attending meetings when the COVID-19 lockdowns commenced in March 2020. The team recognizes the contribution of the consumer representative during the time they were involved and how their influence enhanced the development, design, and implementation of the recruitment phase in particular.

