### Participant Timeline

The trial recruited its first participant in April 2019 and data collection of the last participant was completed in November 2020**.** The study received participants’ health service utilization data in June 2021.

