#### Survey Questionnaires

##### Baseline

The project officers administered a baseline survey to all consented participants. Questionnaires included in the baseline survey are listed in Table 2. Note that the Abbreviated Mental Test Score (AMTS) was administered by a project officer prior to administering the baseline survey. Follow-up questionnaires at the mid-trial point (around 6 months) and end-trial point (around 12 months) included the same battery of questionnaires except for the demographics and AMTS. The baseline survey was delivered to participants during the consent face-to-face meeting and took approximately 45 minutes to complete.

**Table 2 table2:** Survey questionnaires.

Domain	Measure	Context	Score meaning/presentation	Time point		
				Start	Mid	End
Demographic information	Individual questions	Gender, age, weight and height (BMI), occupation, marital status, income, computer skills, social media, and NBN^a^ connectivity	Individual and coded scores	✓		
Cognitive level	Abbreviated Mental Test Score (AMTS) [35]	To establish baseline cognition (10 questions)	Maximum score 10; a score of less than 7 or 8 suggests cognitive impairment	✓		
Impact of care: participant	ACCOM^b^ measure (adapted from ASCOT^c^ for the Australian population) [33]	Self-completion (eight attributes): control over daily life, personal cleanliness and comfort, food and drink, personal safety, social participation and involvement, occupation, accommodation cleanliness and comfort, dignity. Additional questions: subjective rating of health, open question	Four levels: Ideal State, No needs, Some needs, High needs; ASCOT scoring [36]	✓	✓	✓
Health-related quality of life	EQ5D^d^ [37]	Five generic questions on health status: mobility, self-care, usual activities, pain/discomfort, anxiety/depression; respondents’ self-rated health is recorded on a vertical, visual analog scale (VAS: 0-100)	Results presented as an index value (Australian Scoring algorithm); VAS presented as a number from 0 to 100, with 0 indicating the worst and 100 indicating the best imaginable health state	✓	✓	✓
Activities of Daily Living (ADL)	Katz’s ADL [29]	Assesses basic ADLs: feeding, continence, transferring, toileting, dressing, bathing	Maximum score of 6 points indicating fully independent, 4 points indicating moderately impaired, and 2 points indicating severely impaired	✓	✓	✓

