### Strengths and Limitations

To the extent of our knowledge, this is the first large RCT to comprehensively assess the impact of a smart home–based technology on aged care service delivery, quality of life, and public health service costs. However, during the trial, the participants experienced several weeks of lockdowns in March, May, and August of 2020 due to the COVID-19 pandemic. Whether these unprecedented environmental changes had an impact on the study results is yet unknown.

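### All three surveys are analysed together only within each arm; inference should rest on a baseline-adjusted between-arm repeated-measures model, with within-arm change kept descriptive

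*Protocol article*

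**What the plan says.** Survey Data Analyses (protocol article) sets out three steps.

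- At each survey, "intergroup differences in survey results between the intervention and control groups will be analyzed by" chi-square and Wilcoxon rank-sum tests.
- If a difference is significant, a log-binomial regression estimates the groups' relative risk for changes in survey results.
- "Within each group, for all three surveys, the Friedman nonparametric test will be used to understand intragroup differences in survey results". If that is significant, "the Wilcoxon signed-rank test with Bonferroni correction will be used to further investigate pairwise differences between surveys".

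Sample Size states that the power calculation ignored the repeated measures, that these add power, and that suitable techniques will use all available data. Data Collection and Missing Data admits anyone with a baseline and at least one follow-up survey, and allows multiple imputation for missing responses.

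On timing, Participant Timeline says: "The trial recruited its first participant in April 2019 and data collection of the last participant was completed in November 2020". The Baseline section puts the follow-up surveys at around 6 and 12 months. Strengths and Limitations reports that "the participants experienced several weeks of lockdowns in March, May, and August of 2020 due to the COVID-19 pandemic", and adds that any impact on the results is not yet known. Collaborations With Consumers also dates the onset: "when the COVID-19 lockdowns commenced in March 2020".

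**The concern.** The repeated measurements are put to use in the comparison that randomisation does not protect. A within-arm test of change has no concurrent control, so it mixes any treatment effect with ageing, the pandemic and the move from a face-to-face baseline to follow-up preferably by phone. The randomised comparison, which does cancel a shift common to both arms, is left as separate cross-sectional tests without baseline adjustment.

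The Objectives section asks whether the platform can maintain or improve the impact of care. Against that question, a significant decline in the control arm alongside a non-significant one in the intervention arm would look like success, although it is not a test of the difference between arms. The primary instrument also scores social participation and occupation, which lockdowns could plausibly move in both arms.

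**Working it through.** **1. The plan's own sample size.** Inputs from Sample Size: difference 0.08, SD 0.16, alpha 0.05 (two-sided assumed), power 80%, 1:1 allocation. Standardised difference = 0.08/0.16 = 0.5.

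- Two-sample t-test: 63.8, so 64 per arm, total 128.
- Two-sided rank-sum test, with effective n per arm = (N/2)(3/π), noncentrality = 0.5·√(n_eff/2) and df = 2·n_eff − 2: power 0.795 at N = 132 and 0.801 at N = 134.
- Attrition: 134/0.7 = 191.4, so 192; the planned 200 leaves 200 × 0.7 = 140, at least 134.

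The stated 134 is reproduced by a between-arm rank-sum test at a single time point.

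**2. What each planned test uses.**

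| Test | Compares arms | Uses more than one survey | Always run |
|---|---|---|---|
| Chi-square, rank-sum | yes | no | yes |
| Log-binomial | yes | yes, as change | no, after significance |
| Friedman | no | yes, all three | yes |
| Signed-rank | no | yes, pairs | no, after significance |

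No test that is always run both compares the arms and uses the repeated data. The Friedman test also needs all three surveys per person, so it omits people admitted with one follow-up unless imputation supplies the missing survey.

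**3. Calendar.** First recruitment April 2019, last data collection November 2020.

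- 12-month surveys: April 2019 + 12 months = April 2020 at the earliest, up to November 2020. All nominal dates follow the March 2020 onset. No visit window is given, so an early survey in one of the first recruits could precede it.
- Baselines: November 2020 − 12 months = November 2019 at the latest, if the last participant completed 12 months. All precede the onset.
- 6-month surveys: about October 2019 to May 2020. Assume uniform accrual from 1 April to 30 November 2019 (243 days). Surveys due before 1 March 2020 come from the first 153 days: 153/243 = 63%. Surveys due before 31 March 2020 come from the first 182 days: 182/243 = 75%.

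**4. How often the arms disagree when nothing differs.** If each arm's Friedman test rejects with probability p, exactly one of two independent arms rejects with probability 2p(1 − p). This peaks at 50% when p = 0.5. The simulation used 2,000 runs per setting. It assumed no treatment effect, normal scores, the same 12-month shift in both arms with 30% of it present at 6 months, and within-person correlation ρ.

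| n per arm | ρ | Shift (SD) | p | 2p(1 − p) | Simulated disagreement | Rank-sum at 12 months |
|---|---|---|---|---|---|---|
| 67 | 0.5 | 0.2 | 0.220 | 34% | 35% | 4.3% |
| 67 | 0.5 | 0.3 | 0.458 | 50% | 51% | 4.3% |
| 67 | 0.5 | 0.5 | 0.893 | 19% | 20% | 5.3% |
| 97 | 0.7 | 0.2 | 0.496 | 50% | 50% | 5.0% |
| 97 | 0.7 | 0.3 | 0.840 | 27% | 26% | 4.7% |
| 97 | 0.7 | 0.5 | 0.999 | 0.2% | 0.1% | 5.3% |

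Over all eight settings with a shift of 0.2 or 0.3 SD, disagreement runs from 26% to 51%. At 0.5 SD it runs from 0.1% to 20%. With no shift it is about 10%, which is roughly 2 × 0.05 × 0.95. The between-arm test stays at about 4% to 5.5% when a shift is present.

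**5. What omitting the baseline costs.** In a linear model, adjusting for baseline multiplies the variance of the between-arm difference by 1 − ρ². For ρ = 0.5 this is 0.75; for ρ = 0.7 it is 0.51.

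**The case against.** The strongest reply is that the plan never says it will infer a treatment effect from the within-arm tests. Between-arm tests come first, they match the stated N, and the Friedman test is introduced only to understand differences within a group. This stands. A reader might infer that the trial will declare benefit because one arm changed and the other did not, but the article states no such rule, so the 26% to 51% is a risk of misreading and not the plan's error rate. It also lies near the top of the range, and its shifts and correlations are assumed.

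A reader might also infer that every within-arm test is fully confounded with COVID-19, or that all 12-month surveys came after the first lockdown ended. The documents support neither. Most 6-month surveys probably preceded March 2020, and the article gives the onset of the first lockdown but not its end.

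Nor is the within-arm analysis the only one that looks at change: the log-binomial step does so between groups, although conditionally. Multiple imputation may keep people with a missed survey in the Friedman test. The article discloses the lockdowns, and a shift common to both arms does not bias the randomised comparison.

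Model detail may properly be left to an analysis plan that is not shown. That does not answer the point, because the article does name its tests and the named set does not do what Sample Size promises.

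**Conclusion.** The concern holds in a limited form. The survey analysis as stated uses the repeated data jointly only within arms. Its unconditional between-arm tests are cross-sectional and ignore baseline, contrary to the undertaking in Sample Size. Within-arm change cannot show a treatment effect and, from baseline to 12 months, cannot be separated from the onset of the pandemic. That rests on nominal visit dates and on the last participant having completed 12 months. Change from baseline to 6 months is only partly affected. The between-arm tests remain valid against a common shift; what they lose is precision. With assumed correlations of 0.5 to 0.7, baseline adjustment would cut the variance by 25% to 49%.

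**What to change.** Label the Friedman and signed-rank results descriptive and state that no treatment conclusion will be drawn from them or from comparing significance across arms. Base inference on a between-arm repeated-measures model with baseline score, region (the stratification factor), visit and arm-by-visit terms, reporting the arm contrast at each follow-up visit and including everyone with a baseline and at least one follow-up. State that 12-month effects were observed under pandemic conditions.

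A comparison of 6-month surveys before and after March 2020 is exploratory at most. It would have low power with 195 participants, and lockdown exposure at that visit is tied to recruitment order.

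The cost is a change of wording and a little more analysis on data already collected; the Results section says analysis is still under way. The downside is reliance on model assumptions for a bounded score. The planned rank-sum tests can stay as a supporting check.
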